### Secondary outcome measures

#### Safety

Safety will be descriptively analysed based on reported adverse events (AEs) and abnormal laboratory values (biologic AEs) recorded during patient follow-up. Reported AEs and biologic AEs will be graded according to the Common Terminology Criteria for Adverse Events (CTCAE), version 5.0 and reported by the PIs. They will be summarised as the total number of AEs and the percentage of patients with at least one AE for any grade, grades 3–4, grade 5 and related or likely to be related will be given.

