### Site selection and patient enrolment

Sites using Emprint™ or Emprint HP™ as the standard of care for CRLM and meeting a minimum amount of experience (a minimum of 20 ablations of liver tumours using any thermal ablation method per year within the last 4 years) were identified and invited to participate in the study. Centres from 16 European nations (Belgium, Croatia, Denmark, France, Germany, Greece, Italy, the Netherlands, Northern Macedonia, Norway, Portugal, Spain, Sweden, Switzerland, Turkey, and the United Kingdom) were asked to participate.

Patient inclusion and exclusion criteria are displayed in Table 1. Site enrolment started in October 2018 and ended in November 2022. Patient enrolment started in September 2019 and was completed in January 2023.

**Table 1 Tab1:** Patient inclusion and exclusion criteria

Inclusion criteria
18 years old or older
Proven colorectal liver metastases (either histologically or diagnosed by imaging in a patient with known colorectal cancer)
Patient referred to MWA by a multidisciplinary tumour board
Treated with the Emprint or Emprint HP Microwave ablation system
Intention to completely treat (ablation, resection, Stereotactic body radiation therapy [SBRT]) all visible disease within 8 weeks
Max. number of 9 liver lesions
All liver lesions local treatment-naive
Max. diameter of the largest liver lesion treated does not exceed 3 cm

Exclusion criteria
Life expectancy less than 6 months (palliative treatment)
Extrahepatic metastases with the exception of a maximum of 5 lung nodules
Ongoing infection (viral/bacterial)
Patients receiving simultaneous bowel surgery and microwave ablation
Patients receiving simultaneous irreversible electroporation, RFA, SBRT, Cryoablation, high-intensity focused ultrasound, or other local treatment than resection
Pregnancy
Patients with liver metastases that cannot be completely and safely treated
Active cancers other than non-resected primary colon cancer
Advanced liver disease or evidence of liver insufficiency

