### Data collection and quality control

Patients enter the study by accepting participation and signing the informed consent form. Baseline data are collected one month prior to the first treatment (see Fig. 1). Additionally, the relevant data to calculate the baseline Charlson Comorbidity Index (CCI) and the clinical risk score (Fong Score) are collected [18, 19]. After each treatment, technical parameters are collected on how the treatment is performed, whether simultaneous resection of other lesions is performed, and whether concomitant systemic therapy is received. Follow-up data are collected 1 month after the treatment, then every 3 months for the first 12 months and then every 6 months until the study exit or study end, 36 months after the 500th patient has been included. Data for safety and adverse events are collected throughout the whole study. HRQOL data are collected before the first treatment and at the first follow-up.

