## Current status of the study

Between October 2018 and June 2022, 100 hospitals that met the selection criteria were invited, of which 36 were activated (by means of training, access to the database, and eligibility to include patients). As of January 2023, 500 patients have been enrolled with 976 treated tumours, achieving the minimum sample size of 976 lesions for a precision between 0.04 and 0.06. Follow-up data will be collected until January 2026. The final clinical outcome results are expected to be published by 2027.

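### The all-cause adverse event percentages cover a long and unequal follow-up and cannot be read as MWA toxicity; the related-event line helps only in part

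*Protocol article*

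**What the plan says.** The Safety section of the protocol article describes a descriptive analysis of reported AEs and abnormal laboratory values "recorded during patient follow-up". The summary measures are "the total number of AEs and the percentage of patients with at least one AE for any grade", and the sentence goes on: "grades 3–4, grade 5 and related or likely to be related will be given". So there are three all-cause lines (any grade, grades 3–4, grade 5) and one attributed line.

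The section on data collection and quality control sets the period: "Data for safety and adverse events are collected throughout the whole study". Follow-up runs "until the study exit or study end, 36 months after the 500th patient has been included". It also lists what is recorded after each treatment, including "whether simultaneous resection of other lesions is performed, and whether concomitant systemic therapy is received".

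The section on site selection and patient enrolment gives the recruitment dates: "Patient enrolment started in September 2019 and was completed in January 2023". The section on the current status of the study gives the end: "Follow-up data will be collected until January 2026". Table 1 excludes patients who receive another local treatment simultaneously with MWA, except resection.

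**The concern.** The percentage of patients with at least one event is a cumulative quantity. It rises with time under observation, and here that time differs between patients by years. The article itself expects events in this period that are not caused by ablation. Progression, new tumours, death and the start of systemic therapy are all secondary outcomes. Resection may be done in the same session. Abnormal laboratory values count as AEs, and disease or systemic therapy can produce them too.

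The article uses Kaplan–Meier estimates and censoring for its time-to-event outcomes, but for AEs it fixes a crude count and percentage. A reader who took the all-cause lines as the safety of MWA would be reading a figure that depends on length of follow-up, later therapy and the share of combined procedures. It would also compare poorly with series that report a fixed period after ablation.

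**Working it through.** **1. Length of follow-up, from the article's dates.**
- Last patient: January 2023 + 36 months = January 2026, which reproduces the stated end of data collection.
- First patient: September 2019 to January 2026 = 6 years and 4 months = 76 months.
- Potential follow-up is therefore 36 to 76 months. The Abstract ends enrolment in December 2022; with the 36-month rule the range becomes 36 to 75 months, an immaterial difference.
- These are administrative limits. Death, exit and loss to follow-up shorten them, so 36 months is not a minimum for each patient.

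**2. Which lines are affected.**
- Any grade, grades 3–4 and grade 5: all causes, all of follow-up. They take in events from every source named above.
- Related or likely related: meant to exclude background events. The Safety section does not say what the event must be related to. After a session that combines ablation and resection, an event caused by the resection could be counted or not, depending on how the site reads the term.

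**3. Illustration of the time dependence.** The article gives neither AE rates nor the share of sessions with resection, so every rate here is an assumption. Let p0 be the peri-procedural risk, r a constant background rate and t the time; ignore death and exit.

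Cumulative percentage = 1 − (1 − p0) × exp(−r × t)

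With p0 = 5% and r = 0.2 per patient-year:
- 3 months: 1 − 0.95 × exp(−0.05) = 9.6%
- 36 months: 1 − 0.95 × exp(−0.6) = 47.9%
- 76 months: 1 − 0.95 × exp(−1.267) = 73.2%

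Over p0 = 5–10% and r = 0.05–0.40 per patient-year, the range is 6–19% at 3 months, 18–73% at 36 months and 31–93% at 76 months.

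A second set of assumptions looks at background events alone (p0 = 0) at 0.5–2% per month, with 1 − exp(−r × t):
- 1 month: about 0.5–2%
- 36 months: 1 − exp(−0.18) = 16% to 1 − exp(−0.72) = 51%
- 76 months: 1 − exp(−0.38) = 32% to 1 − exp(−1.52) = 78%

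Both sets show the same pattern: over years of follow-up, background events can make up most of an all-cause percentage. Because early exit is ignored, the figures for 36 and 76 months are high for a real cohort at the same rates. Neither calculation says anything about the related-event line, which is designed to leave background events out.

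**4. Can the sources be separated?** Yes, for the two main co-treatments. Simultaneous resection and concomitant systemic therapy are recorded after each treatment. The summary described in the Safety section does not use them.

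**The case against.** The strongest reply is that the same sentence pre-specifies a related-event line, so a treatment-attributed summary exists. This stands. A reader might infer that none of the planned percentages measures MWA toxicity, or that the safety result can support no statement about MWA. The article does not bear that out: the criticism fits the three all-cause lines, and the related line only to the extent that its target is undefined.

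A second reply is that risk windows, per-session tables and displays by co-treatment are commonly left to the full protocol or the SAP, which are not shown. This stands too: their absence from an article is not an error, and nothing in the Safety section rules them out. What remains is that the article does fix a measure, a crude percentage over all of follow-up, and that measure is open to misreading.

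Third, a reader might infer that patients who die early simply look safer. That goes too far, because a fatal AE is counted under grade 5 and overall survival is a separate outcome. Early exit shortens exposure, which is a reason for person-time rates, but fatal events are not hidden.

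Fourth, site attribution without source verification is a limitation that the article discloses, and a time window would rest on site-entered onset dates that are equally unverified. This is fair. A window does not remove that weakness; it removes the dependence on length of follow-up.

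Finally, the analysis is descriptive and no decision rule rests on it. That sets the weight of the point but does not remove it.

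**Conclusion.** The point holds as a minor improvement. The any-grade, grade 3–4 and grade 5 percentages, which include abnormal laboratory values, cover a potential 36 to 76 months, shortened by death or exit. They mix MWA toxicity with later systemic therapy, progression and simultaneous resection, and should not be read as MWA toxicity. The related-event line mitigates this in part; its weakness is that it does not say whether the reference is MWA or the whole procedure including resection.

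The range of follow-up comes from the article's own dates. The size of the distortion cannot be derived from the article: the percentages in the working depend wholly on assumed constant rates with no death or exit, and show direction and plausible scale only. The primary outcome and the sample size are not affected.

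**What to change.** - Add a peri-procedural AE summary, for example events with onset within 30 days of each MWA session, per session and per patient, by grade and relatedness. The 30 days are an example of a reporting window, not a figure from the article; the sponsor should choose the window and state it before the final analysis.
- Show this summary separately for MWA alone and MWA with simultaneous resection, and by concomitant systemic therapy, using the fields already recorded after each treatment.
- State that relatedness means relatedness to MWA.
- Present this summary and the related-event line as the main safety result.
- Keep the whole-follow-up table and add person-time rates, so that late complications remain visible and unequal follow-up is accounted for.

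The cost is a few extra tables from AE onset dates and existing treatment-form fields. If sites have recorded relatedness without a defined reference, a clarification through the existing query process may be needed. The one drawback is that late MWA complications fall outside the windowed table; the related-event line and the whole-follow-up table cover them.

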#### Time-to-event

The first MWA treatment will be the starting point for the per-patient time-to-event analyses, and the first MWA treatment of the respective lesion for per-lesion time-to-event analyses. OS is defined as the time of death of any cause, for DFS as the time of any progression, new tumours, or death, for HDFS as the time of any progression of liver tumours, new tumours in the liver or death and for time to progression untreatable by thermal ablation as the time of progression of a treated tumour that has been determined as not treatable by thermal ablation according to the investigator. Systemic cancer therapy vacation is defined as the time between the first MWA treatment and the start of systemic cancer therapy. In these analyses, subjects lost to follow-up will be censored at the last recorded communication with the patient.

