**Fig. 1 Fig1:**
[figure not shown]
Flowchart detailing the data collected at each stage of the enrolment. ECOG: Eastern Cooperative Oncology Group; CCI: Charlson Comorbidity Index

Data validity, completeness, consistency, and uniformity are warranted by case report forms with programmed constraints on data types, ranges, and mandatory data fields. Furthermore, a regular remote monitoring scheme is employed to verify the data quality, inclusion of patients, and follow-ups. No on-site monitoring or source data verification is performed due to resource limitations. Remote monitoring is performed quarterly. Activities include monitoring calls with the sites, sending query reports and monitoring call reports in which all necessary action points are documented. Data are monitored regularly, and queries are raised via the electronic data capturing system. The non-interventional nature of the study means that the exact dates of the procedures and follow-ups are determined by the medical team.

The electronic data collection system was developed and supported by OpenClinica (LLC, Waltham, MA, USA).

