### Primary outcome measure

The primary outcome measure is the local control rate for all ablated tumours at 1 year (defined as fully ablated with no evidence of disease within the ablation zone at 12 months + / − 45 days after the last ablation of the respective tumour) as assessed by the investigatorsʼ routine protocols (Table 2).

**Table 2 Tab2:** Primary and secondary outcome measures

	Outcome measure	Measured according to	Definition
*Primary outcome measure*			
Effectiveness	Local tumour control at 12 months on a per lesion basis	Investigator assessment	Tumour is considered to be fully ablated with no evidence of disease within the ablation zone at 12 months + / − 45 days after the last ablation
*Secondary outcome measures*			
Safety	Adverse events	CTCAE V5.0	
Effectiveness	Overall survival	Investigator assessment	Time between the first treatment and the time of death of any cause
	Overall disease-free survival	Investigator assessment	Time between the first treatment and the time of any progression, new tumours, or death
	Hepatic disease-free survival	Investigator assessment	Time between the first treatment and the time of any progression of hepatic tumours, new hepatic tumours or death
	Time to untreatable progression by thermal ablation	Investigator assessment	Time between the first treatment and the time of progression of a treated tumour that has been determined as not treatable by thermal ablation
	Systemic cancer therapy vacation	Investigator assessment	Time between the first treatment and the start of systemic cancer therapy
	Quality of Life	EORTC QLQ-C30	

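### Censoring patients lost to follow-up at last communication suits OS, but biases DFS, hepatic DFS and the other progression-based secondary curves upward whenever contact outlasts disease assessment

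*Protocol article*

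**What the plan says.** The Time-to-event section of the protocol article defines all the outcomes together and then gives a single rule for these analyses: "subjects lost to follow-up will be censored at the last recorded communication with the patient". The outcomes it covers have different kinds of event:

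- OS: "OS is defined as the time of death of any cause".
- DFS: "for DFS as the time of any progression, new tumours, or death". Table 2 agrees: "Time between the first treatment and the time of any progression, new tumours, or death".
- Hepatic DFS: "for HDFS as the time of any progression of liver tumours, new tumours in the liver or death".
- Time to progression untreatable by ablation: "the time of progression of a treated tumour that has been determined as not treatable by thermal ablation according to the investigator". Death is not an event here.
- Per-lesion time-to-event analyses, which start at the first ablation of the lesion concerned.

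Table 2 gives investigator assessment as the source for all the effectiveness outcomes. Follow-up is at 1 month, then 3-monthly to 12 months, then 6-monthly. The Data collection and quality control section adds that "the exact dates of the procedures and follow-ups are determined by the medical team". The Missing data section ties drop-out to lesion follow-up at 12 months ± 45 days and plans a sensitivity analysis, but only for the primary outcome.

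**The concern.** A censoring date should be the last date on which the patient was known to be free of the event. For death, that is the last contact. For progression or a new tumour, it is the last disease assessment, because a contact without one says nothing about whether disease has returned. A patient last assessed at month 12 and last in contact at month 24 would be counted as progression-free for 12 months in which progression could not have been found.

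Such patients stay in the Kaplan–Meier and Cox risk sets without being able to contribute a progression event. The estimated hazard falls and the curve rises, never the reverse. The affected outcomes are secondary, but they are the ones that describe the longer-term durability of ablation.

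**Working it through.** **Plan's own figure.** The article gives no figure for the time-to-event outcomes. Its one design figure, 0.057, is the full width of the Wilson interval for the primary proportion (0.0572 for 750 lesions at 0.8). This point does not touch it.

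**Mechanism.** If a fraction u of the risk set is in contact but no longer assessed, the observed progression hazard is λ(1 − u), so the curve estimates exp(−λ(1 − u)t). With λ = 0.05 per month and t = 24 months:

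- u = 0: exp(−1.20) = 0.301
- u = 0.05: exp(−1.14) = 0.320, which is 1.9 points too high
- u = 0.10: exp(−1.08) = 0.340, which is 3.8 points too high

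**Simulation inputs.** From the article: the visit schedule and the censoring rule. Assumed, because the article gives no values: exponential progression at 0.05 per month; visits within ±1 month of schedule; 20% of patients stopping imaging at a time uniform over months 0 to 24, unrelated to prognosis; contact continuing for a further gap of 0, 3, 6 or 12 months. Progression is dated at the visit that finds it. There are 400,000 patients per row.

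24-month event-free survival, progression events only:

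| Gap (months) | Complete follow-up | Last communication | Last imaging | Inflation against complete follow-up |
|---|---|---|---|---|
| 0 | 35.8% | 35.8% | 35.1% | 0.0 points |
| 3 | 35.8% | 36.8% | 35.0% | 1.1 points |
| 6 | 35.7% | 37.8% | 35.0% | 2.1 points |
| 12 | 35.9% | 39.8% | 35.2% | 3.9 points |

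(Inflation is computed before rounding.) The complete-follow-up value exceeds 30.1% because about half of the month-24 visits fall after month 24: (exp(−0.90) + exp(−1.20))/2 = (0.407 + 0.301)/2 = 0.354, close to the simulated 35.8%.

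**Variations.**

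- Deaths at an assumed 0.01 per month counted as events and seen while contact lasts, as for DFS: inflation is 0.0, 0.8, 1.7 and 3.0 points for gaps of 0, 3, 6 and 12 months.
- 10% stopping imaging, progression only: 0.5, 1.0 and 1.9 points for gaps of 3, 6 and 12 months. With 30% stopping: 1.8, 3.3 and 6.0 points.
- Gap counted from the last scan performed instead of from the time imaging stops (20% stopping): 0.2, 1.3 and 3.5 points.
- A second set-up, with median time to progression 12 months, visits exactly on schedule, 5% to 20% lost per year, and deaths after loss not counted: 24-month inflation is 0 with no gap, 0.01 to 0.02 at 3 months, 0.01 to 0.04 at 6 months and 0.02 to 0.08 at 12 months. For example, with 10% lost per year and a 6-month gap, survival is 0.272 under the rule and 0.252 with last-imaging censoring.

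**The alternative rule.** Last-imaging censoring runs about 0.7 points low in the first set-up and matches complete follow-up within about 0.002 in the second. It is therefore close to neutral but not exact.

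**The case against.** The strongest reply is that the gap is assumed. The rule applies only to patients lost to follow-up. The article describes no contact with patients outside scheduled follow-up; the calls it mentions are monitoring calls with sites. The last recorded communication may simply be the last visit, with an assessment, and then the two dates coincide and nothing is inflated. That medical teams set the dates does not show that imaging lapses while contact continues. All of this stands. It limits the size of the bias, but it does not make the rule right when the dates differ.

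A second reply is that the bias is small beside sampling error. With 500 patients and survival near 35%, the 95% half-width is 1.96 × √(0.35 × 0.65/500) = 0.042, about 4 points. The outcomes are secondary, there is no comparison arm, and no confirmatory testing is planned. This also stands, and it keeps the point from being critical. But the bias runs in one direction and the interval does not allow for it.

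A third reply is that outcome-specific censoring dates are often left to an analysis plan, which is not shown here. That would answer a silence. Here the article states a rule and applies it to all these analyses.

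A reader might infer more than the documents support: that every censored patient is affected, that long contact without imaging will be common, or that DFS will be overstated by 4.6 points. The article states the rule only for patients lost to follow-up and gives no loss or contact pattern. The 4.6 points (39.7% against 35.1%) needs a 12-month gap, leaves out death as a DFS event, and uses a comparator that itself runs slightly low.

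**Conclusion.** Wrong as written for DFS, hepatic DFS, time to progression untreatable by ablation and the per-lesion progression analyses; suitable for OS. The direction is certain wherever contact outlasts assessment. The size is modest and cannot be derived from the documents. With a hazard of 0.05 per month and 20% stopping imaging within 24 months, 24-month inflation is nil without a gap and about 1 to 4 points for gaps of 3 to 12 months. It falls to about 1 to 3 points when deaths at 0.01 per month count as events. That relief does not apply to time to untreatable progression, where death is not an event. The figures also assume that stopping imaging is unrelated to prognosis. The primary 12-month proportion has its own assessment-based drop-out rule and is unaffected. Nothing is claimed here about systemic therapy vacation.

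**What to change.** Keep last communication as the censoring date for OS. For DFS, hepatic DFS, time to progression untreatable by ablation and the per-lesion progression analyses, censor patients or lesions without an event at the last disease assessment, meaning liver imaging for the hepatic and lesion outcomes. Report last-communication censoring as a sensitivity analysis, so that readers can see how much the choice matters.

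This takes one sentence and can be settled before the final analysis, whose results are expected by 2027. The costs are slightly less follow-up time and slightly less favourable curves. It also relies on assessment dates being recorded at follow-up, which is likely but not stated in the text shown and should be confirmed first.
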